## Abstract

**Background:**

Provision of essential newborn care at home, rapid identification of illness, and care-seeking by caregivers can prevent neonatal mortality. Mobile technology can connect caregivers with information and healthcare worker advice more rapidly and frequently than healthcare visits. Community health workers (CHWs) are well-suited to deliver such interventions. We developed an interactive short message service (SMS) intervention for neonatal health in Kenya, named CHV-NEO. CHV-NEO sends automated, theory-based, actionable, messages throughout the peripartum period that guide mothers to evaluate maternal and neonatal danger signs and facilitate real-time dialogue with a CHW via SMS. We integrated this intervention into Kenya’s national electronic community health information system (eCHIS), which is currently used at scale to support CHW workflow.

**Methods:**

The effect of CHV-NEO on clinical and implementation outcomes will be evaluated through a non-blinded cluster randomized controlled trial. Twenty sites across Kisumu County in Western Kenya were randomized 1:1 to provide either the national eCHIS with integrated CHV-NEO messaging (intervention) or standard of care using eCHIS without CHV-NEO (control). We will compare neonatal mortality between arms based on abstracted eCHIS data from 7200 pregnant women. Secondary outcomes include self-reported provision of essential newborn care (appropriate cord care, thermal care, and timely initiation of breastfeeding), knowledge of neonatal danger signs, and care-seeking for neonatal illness, compared between arms based on questionnaires with a subgroup of 2000 women attending study visits at enrollment in pregnancy and 6 weeks postpartum. We will also determine CHV-NEO’s effect on CHW workflows and evaluate determinants of intervention acceptability, adoption, and fidelity of use through questionnaires, individual interviews, and messaging data.

**Discussion:**

We hypothesize that the CHV-NEO direct-to-client communication strategy can be successfully integrated within existing CHW workflows and infrastructure, improve the provision of at-home essential newborn care, increase timely referral of neonatal illness to facilities, and reduce neonatal mortality. The intervention’s integration into the national eCHIS tool will facilitate rapid scale-up if it is clinically effective and successfully implemented.

**Trial registration:**

ClinicalTrials.gov, NCT05187897. The CHV-NEO study was registered on January 12, 2022.

## Administrative information

Note: the numbers in curly brackets in this protocol refer to SPIRIT checklist item numbers. The order of the items has been modified to group similar items (see http://www.equator-network.org/reporting-guidelines/spirit-2013-statement-defining-standard-protocol-items-for-clinical-trials/).

## Introduction

### Background and rationale {6a}

Despite recent reductions in under-five mortality, neonatal mortality (i.e., mortality in the first 28 days of life) remains high in low- and middle-income countries (LMICs). For neonates who come home after facility delivery, subsequent deaths are the result of complications of preterm delivery and neonatal infections [1]. For each of these causes of death, evidence-based prevention and management strategies exist [2, 3]. Early initiation of breastfeeding (in the first hour of life) and exclusive breastfeeding (EBF) are independently associated with lower neonatal mortality [4]. Clean cord care can prevent cord infections, sepsis, and neonatal mortality [5, 6]. Thermal care, including skin-to-skin contact with the mother, drying and wrapping immediately after birth, and delaying bathing for at least 24 h, prevents hypothermia and associated morbidity and mortality, particularly in preterm babies [7]. The World Health Organization (WHO) recommends home implementation of thermal care [8]. Despite evidence for the efficacy of these interventions, coverage remains low in many African settings [9–12]. Caregiver provision of essential newborn care (ENC) at home requires accurate information, motivation, behavioral skills, and an enabling environment [13].

When neonates develop illness, timely and appropriate care-seeking is essential for survival. Many newborns continue to die at home without health care being sought because of delays that prevent postpartum women and neonates from accessing the care they need. The “three delays model,” originally developed to understand maternal deaths [14], has been adapted to assess missed opportunities leading to neonatal deaths. The model identifies delays in (1) identifying illness and deciding to seek care, (2) reaching the health facility, and (3) receiving quality care once a facility is reached. Prior studies suggest delays recognizing illness and deciding to seek care (delay 1) account for up to 80% of neonatal and child deaths [15–18].

Community health workers (CHWs) are a large cadre of community-based lay health workers that conduct home visits in pregnancy and the neonatal period, provide preventative care, health education, and referrals to seek care when needed. Home visits by CHWs supplement facility-based care and promote family contact with the health system at crucial times. A number of studies in LMIC settings demonstrate that home-based neonatal care by trained CHWs can significantly increase ENC [19–21], improve the identification of neonatal illness [20–22], facilitate referrals, and ultimately prevent neonatal mortality [23, 24]. Although the provision of home-based care by CHWs has demonstrated a positive impact, it is limited by the fact that visits are intermittent. Despite recommendations of one to four home visits in the early neonatal period, CHWs have difficulty meeting their visit goals due to access challenges in large catchment areas and lack of knowledge, supervision, and motivation [21, 25, 26]. In addition, CHWs are not “on-call” and intermittent visits may miss critical periods when neonates become ill and quickly decline.

Mobile health (mHealth) interventions are increasingly used in a variety of contexts to supplement healthcare provider encounters with more frequent, on-demand, and anticipatory guidance. In Kenya, for example, the National Community Health Digitization Strategy 2020–2025 launched an effort to digitize community health services across the country so that CHWs use a tablet-based electronic community health information system (eCHIS) to manage service delivery and data capture [27]. According to the Communications Authority of Kenya, there are now 46 million phone subscriptions in Kenya, for a national population of 43 million [28]. Short messaging service (SMS) is an accessible modality that can be used to educate, provide reminders, and improve communication between healthcare workers and patients [29–32]. There is also evidence that mHealth interventions improve antenatal care (ANC) and PNC attendance, skilled delivery uptake, and EBF [33–37]. Few studies have evaluated neonatal outcomes [38].

We previously developed an interactive, semi-automated SMS intervention that connects perinatal clients with nurses, named Mobile WACh [39]. Mobile WACh message content has been adapted for a variety of maternal and child health outcomes and shown in randomized studies to increase the duration of EBF and postpartum uptake of contraception [37, 40]. An ongoing trial evaluates the efficacy of the approach in improving neonatal outcomes [41]. However, no studies have evaluated the integration of Mobile WACh into routine service delivery or tested intervention delivery by CHWs.

### Objectives {7}

CHV-NEO integrates Mobile WACh into Kenya’s national eCHIS, resulting in an interactive SMS intervention that connects perinatal clients with CHWs. Our objective is to pragmatically evaluate: (1) the effect of CHV-NEO on neonatal mortality, ENC provision, and care-seeking; (2) the effect of CHV-NEO on CHW service delivery outcomes; and (3) levels and determinants of CHV-NEO implementation outcomes. We hypothesize that mother–infant dyads at facilities randomized to CHV-NEO will demonstrate lower neonatal mortality, higher provision of ENC, and higher facility care-seeking compared with standard of care and that frequency of CHW routine home visits will not differ between arms.

### Trial design {8}

This study is a non-blinded cluster-randomized controlled superiority trial comparing two parallel arms (intervention vs. control). The study intervention is delivered by CHWs who are employed by Kisumu County and whose work takes place at the household and community level. Each CHW is assigned by the county to a community area for which they are responsible. Each CHW is affiliated with and supervised through a nearby assigned healthcare facility. The unit of randomization in our trial is the healthcare facility and the associated CHWs and community areas, referred to here as “facility clusters”. Twenty clusters were randomized to the intervention (eCHIS with integrated SMS, referred to as CHV-NEO) or the control (routine eCHIS without SMS) in a 1:1 allocation ratio (10 control clusters, 10 intervention clusters). All CHWs linked to each facility cluster provide the assigned intervention to their community-based clients.

## Methods: participants, interventions, and outcomes

### Study setting {9}

This study takes place in community areas linked to 20 government healthcare facilities in Kisumu County, Kenya. Kenya has approximately 30,000 neonatal deaths each year [42], with a neonatal mortality rate of 21.0 per 1000 live births in Kisumu [43]; this is substantially higher than Sustainable Development Goal 3 of ≤ 12 neonatal deaths per 1000 live births by 2030 [44]. Facilities were selected to include a diversity of characteristics, including rural and urban location, a range of facility levels from health centers (level 3) to county hospitals (level 5), and patient volumes of 100–1000 monthly antenatal care visits.

### Eligibility criteria {10}

The study enrolls four groups of participants to evaluate different outcomes: pregnant women for a mortality cohort, pregnant women for an in-depth data collection cohort, CHWs, and CHW supervisors.

#### Pregnant women—mortality cohort

Outcomes are ascertained from two nested cohorts of pregnant women (Fig. 1). The primary clinical effectiveness outcome (neonatal mortality) is ascertained using abstracted routine data from the eCHIS platform in all study sites. Inclusion criteria for these women are being registered as pregnant in eCHIS at gestational age ≤ 36 weeks by a CHW linked to a study facility.

**Fig. 1 Fig1:**
[figure not shown]
Study design overview

#### Pregnant women—in-depth cohort

Secondary clinical outcomes and implementation outcomes are ascertained among a nested cohort of women recruited by the study team when attending ANC visits at study facilities. Eligible participants for this cohort are pregnant (26–36 weeks gestation); registered as pregnant in eCHIS by a CHW linked to the study facility; age ≥ 14; receiving ANC at a study facility; able to read and respond to text messages in English, Kiswahili, or Luo or have someone in the household who can assist; have daily access to a mobile phone (own or shared) on Safaricom or Airtel networks; and plan to be in the area for at least 3 months postpartum. Participants who are enrolled in another research study or have previously been enrolled in CHV-NEO in a prior pregnancy are excluded.

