#### SMS curriculum

The CHV-NEO SMS intervention is based on the content of the Mobile WACh NEO intervention [41], with adaptations for this study guided by input from perinatal clients, nurses, CHWs, and CHW supervisors in formative interviews and focus groups. The intervention is based on the Information, Motivation, Behavioral skills model of behavioral change [47], with the goal of improving the provision of preventative ENC, identification of illness, and care-seeking if needed (Fig. 2). Clients receive a curriculum of pre-composed SMS messages automatically sent on a schedule starting at 28 weeks gestation and extending until 6 weeks postpartum. Clients can send an SMS at any time and their message will be read and manually responded to by the CHW who routinely conducts their home visits. Automated messages are sent in English, Luo, or Kiswahili depending on the participant’s preference. Sending and receiving SMS is at no cost to the participant or the CHW.

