**Fig. 2 Fig2:**
[figure not shown]
Intervention conceptual framework

Automated SMS topics and schedule are summarized in Fig. 3, based on the client’s gestational age, date of delivery, and delivery outcome, obtained from eCHIS. From enrolment until 38 weeks gestation, automated SMS are sent weekly, encouraging facility delivery and birth planning, and providing anticipatory guidance about neonatal danger signs and emotional support. From 38 weeks gestation until delivery, automated SMS are sent daily, with similar content and highlighting neonatal danger signs and ENC practices, including immediate and exclusive breastfeeding, thermal, and cord care. From delivery to 2 weeks postpartum, two messages are sent per day: one message with screening questions regarding neonatal danger signs and encouragement to message if they have a concern and one message with educational content on postpartum care and complications, ENC practices, and emotional support. From 2 to 6 weeks postpartum, SMS are delivered every other day. Additionally, based on input from perinatal clients, CHWs, and policymakers in formative design activities, clients receive a reminder message when they are referred to the healthcare facility by the CHW, when they are due for their 6-week postpartum facility visit, and when a CHW is scheduled to conduct a home visit. All messages open with the participant’s name, state that the message is from their CHW, and contain a question to engage women in conversation. Clients who deliver a preterm or low birthweight baby receive a modified track of messages, which includes information about additional care for small and preterm babies, including Kangaroo Mother Care. Clients who experience a stillbirth or neonatal death receive a 4-week curriculum of weekly bereavement messages which provide condolences and emotional support; messages related to the infant are stopped. The message bank is available upon request.

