#### Integration of SMS into *eCHIS* application

In partnership with the Kenyan Ministry of Health, SMS messaging functionality was integrated into the eCHIS software platform as a module of the existing interface (Fig. 4). Consenting and enrollment to communicate by SMS with the CHW was added as a required step in the standard antenatal home visit workflow among intervention CHWs, and an additional functionality was added to update client phone number, SMS language, or messaging preferences after enrollment as needed. Templates for CHW replies to frequently asked client questions were incorporated as a “FAQ” module with a topically organized bank of editable message templates in English, Swahili, and Luo (Fig. 4).

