#### Quantitative questionnaires

Quantitative questionnaires are administered electronically to women, CHWs, and supervisors by study staff using the REDCap platform. Women complete questionnaires during study visits at the facility at enrollment in pregnancy and at 6 weeks postpartum (Table 2). At each visit, a standardized questionnaire is administered to record self-reported outcomes and sociodemographic and clinical characteristics that may be associated with them. Outcomes include timing of breastfeeding initiation, introduction of complementary foods, application of substances to the umbilical cord, knowledge of eight danger signs (not feeding, high temperature, low temperature, fast breathing, difficulty breathing, not moving, convulsions, and jaundice) [53], timing of first bath, attending facility-based care during illness episodes, and acceptability of CHV-NEO, using the AIM [48]. Associated demographic and clinical factors include maternal education, income, employment, parity, distance from home to clinic, intimate partner violence, depression symptoms, past healthcare experience, parental self-efficacy, and infant sex.

CHWs and supervisors complete questionnaires annually: at study launch, 1 year, and study close (Table 2). Questionnaires include outcomes as well as demographic and professional characteristics that may be associated with outcomes. Outcomes include acceptability of CHV-NEO, assessed using the AIM measure [48], and time spent on work duties in the prior 2 weeks. Characteristics that may be associated with outcomes include professional background, training, and experience and comfort with the eCHIS platform.

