### Statistical methods

#### Statistical methods for primary and secondary outcomes {20a}

Statistical analysis approaches for each outcome are summarized in Table 1. Analysis of primary and secondary outcomes will be by intention-to-treat. If participants relocate between facilities in different intervention arms during the course of the study, the original assignment is used in the analysis. For analyses that include random effects at the CHW level, if a participant’s assigned CHW changes, their data is analyzed under the CHW under whose care they are for the longest proportion of follow-up time preceding outcome ascertainment. Analyses will be adjusted for any baseline characteristics that differ significantly between study arms.

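### Many intervention-arm enrolment questionnaires in the in-depth cohort may follow the start of SMS, yet the adjustment rule is not limited to characteristics that SMS cannot change

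*Protocol article*

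**What the plan says.** - **Who is enrolled and when.** The in-depth cohort criteria state: "Eligible participants for this cohort are pregnant (26–36 weeks gestation); registered as pregnant in eCHIS by a CHW linked to the study facility". Under Recruitment {15}, women enter eCHIS through the CHWs' routine home visits.
- **How SMS begins.** For intervention CHWs, the section on integrating SMS into eCHIS says: "Consenting and enrollment to communicate by SMS with the CHW was added as a required step in the standard antenatal home visit workflow". The SMS curriculum section describes messages "automatically sent on a schedule starting at 28 weeks gestation and extending until 6 weeks postpartum". It adds: "From enrolment until 38 weeks gestation, automated SMS are sent weekly". These antenatal messages include material "providing anticipatory guidance about neonatal danger signs and emotional support".
- **When the baseline questionnaire is given.** Table 2 places baseline ascertainment at the enrolment visit, under the column group for the period after intervention deployment.
- **What is recorded.** The Quantitative questionnaires section describes a questionnaire at each visit. It lists outcomes, including danger-sign knowledge, separately from associated factors, which end with "intimate partner violence, depression symptoms, past healthcare experience, parental self-efficacy, and infant sex".
- **How it is used.** Statistical methods {20a} states: "Analyses will be adjusted for any baseline characteristics that differ significantly between study arms".

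The protocol gives neither the distribution of gestational age at enrolment nor SMS uptake before the study visit.

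**The concern.** A covariate is safe to adjust for when treatment cannot have altered it. Here the window for collecting baseline data overlaps the intervention, and SMS sign-up runs through the CHW rather than through study enrolment. For some intervention women, the answers labelled baseline will have been given after weeks of messages.

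The adjustment rule accepts any characteristic that differs significantly, so a difference produced by SMS could itself bring the variable into the model. That is separate from the usual objection to testing chance imbalance, because part of the difference may be a treatment effect. Conditioning on it would remove the part of the effect that passes through that variable. The outcomes exposed are the secondary ones: breastfeeding initiation, cord and thermal care, danger-sign knowledge and care-seeking. A baseline table could also present an early effect as imbalance between arms.

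**Working it through.** **1. Does SMS wait for study enrolment?** Nothing says so. SMS sign-up is a step in the CHW's workflow, while study recruitment takes place at ANC. Withdrawal from SMS and withdrawal from the study are independent of each other ({11b}). The mortality cohort (7200 across both arms) is far larger than the in-depth cohort (2000), so most SMS clients never have a study visit. Enrolment in the weekly-message sentence is therefore most naturally SMS enrolment.

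**2. Share of enrolment visits at or after 28 weeks.** The window is 26–36 weeks and SMS starts at 28. Uniform enrolment gives (36 − 28)/(36 − 26) = 0.80. Other patterns, assumed as 26 + 10 × Beta(a,b), give:
- late, Beta(2,1): 1 − 0.2² = 0.96
- mid-window, Beta(2,2): 0.90
- early, Beta(1,2): 0.8² = 0.64
- earlier, Beta(1,3): 0.8³ = 0.51
- concentrated near 26–28 weeks, Beta(1,4): 0.8⁴ = 0.41

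Each share is multiplied by the proportion u already signed up for SMS. Under uniform enrolment, the exposed share passes one half only if u > 0.5/0.8 = 62.5%.

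**3. Dose before enrolment.** With uniform enrolment, full uptake and weekly messages from 28 weeks, exposed women average (1 + 2 + … + 8)/8 = 4.5 automated messages. Over all intervention women this is 0.8 × 4.5 = 3.6. The whole curriculum, assuming delivery at 40 weeks, is about 10 weekly + 14 daily + 28 (two a day for 2 weeks) + 14 (alternate days for 4 weeks) = 66. So 3.6/66 is about 5%. Exchanges with the CHW come on top.

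**4. The plan's own power figure.** Sample size {14} states 80% power for 50% vs 72%, with 10 clusters per arm, coefficient of variation k = 0.25 and 10% attrition (m = 100 × 0.9 = 90). The formula is c = 1 + (z₀.₉₇₅ + z₀.₈)² × [p₀(1−p₀)/m + p₁(1−p₁)/m + k²(p₀² + p₁²)]/(p₀ − p₁)².
- The bracket is 0.00278 + 0.00224 + 0.04803 = 0.05304.
- c = 1 + 7.849 × 0.05304/0.0484 = 9.60, so 10 clusters per arm. Power with 10 is 81.7%, and the stated figure reproduces.

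**5. Illustrative over-adjustment for the newborn-care outcomes.** Points removed = exposed share × shift in covariate (SD) × outcome slope (points per SD). With assumed shifts of 0.1–0.5 SD and slopes of 3–10 points:
- low: 0.8 × 0.1 × 3 = 0.24 of 22 points (about 1%)
- high: 0.8 × 0.5 × 10 = 4.0 of 22 points (about 18%)

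Putting the reduced difference into the formula in step 4, a loss of 2 points (50% vs 70%) gives power of about 75%, and a loss of 4 points (50% vs 68%) about 68%.

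**6. Danger-sign knowledge, if it is asked at enrolment.** The planned difference is 0.4 signs (2.0 vs 2.4).
- With an assumed shift of 0.1–0.2 signs and a slope of 6-week on enrolment knowledge of 0.3–0.5, adjustment removes 0.1 × 0.3 = 0.03 to 0.2 × 0.5 = 0.10 signs, or 7.5–25%.
- If the shift is instead proportional to dose, it is 0.4 × 3.6/66 = 0.022 signs. The loss is then 0.022 × 0.3 to 0.022 × 0.5 = 0.007–0.011 signs, about 2–3%.
- Adjustment also has to be triggered. The plan's figures imply a standard error of about 0.4/(2.24 + 0.84) = 0.13. If enrolment knowledge has similar variance and the test respects clustering, a true shift of 0.1 reaches p < 0.05 with probability about Φ(0.1/0.13 − 1.96) = 12%, and a shift of 0.2 about Φ(0.2/0.13 − 1.96) = 34%. A test that ignored clustering would trigger more often; the protocol does not say which is meant.

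**The case against.** The strongest reply is that few usable covariates are at risk and the early dose is small.

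- **Which covariates.** Education, income, parity, distance and infant sex cannot plausibly be moved by text messages. The described curriculum does not address partner violence, discussion of mental health was removed from it, and past healthcare experience is largely retrospective. That leaves mainly parental self-efficacy and, through supportive wording, depression symptoms. This stands.
- **Danger-sign knowledge.** A reader might infer that it is a baseline covariate because outcomes are said to be recorded at each visit. The text does not support that. The same outcome list contains first bath and cord applications, which cannot be asked in pregnancy, so the list pools both visits. Knowledge is also listed as an outcome, not an associated factor, and is defined at 6 weeks.
- **Dose and trigger.** A reader might infer that the rule picks out exactly what SMS has shifted, or that 8–25% of the knowledge effect is lost. Both go too far: about four weekly messages precede enrolment, and shifts of 0.1–0.2 signs would usually not reach significance under a test that respects clustering.

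The dose argument has limits of its own. The protocol says that antenatal guidance on trial outcomes, danger signs in particular, was made more frequent, and clients may message the CHW at any time. A count of automated messages may therefore understate early exposure. None of this alters the rule, which is open to any characteristic. The statistical analysis plan is not shown, but one that restricted the covariates would depart from this sentence.

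**Conclusion.** The point holds as a defect in a stated rule. The enrolment window and the messaging period overlap, SMS sign-up does not wait for the study visit, and the rule can condition on values that SMS may already have changed. The likely direction is towards no effect.

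The size is unknown and probably small. It rests on gestational age at enrolment, prior uptake, covariate shifts and slopes, none of which the protocol gives. The illustrations run from about 1% to 18% of the planned 22-point difference, and only if the covariate is measured at enrolment and the rule is triggered.

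Two stronger readings are not supported. A reader might infer that most intervention-arm baselines follow exposure. That is true under uniform or later enrolment with high uptake, but fails if enrolment concentrates at 26–28 weeks or if uptake is below 62.5% under uniform enrolment. A reader might also infer that the primary outcome is compromised. Mortality comes from de-identified eCHIS data, so these questionnaire covariates do not enter it, and only the secondary outcomes are at issue.

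**What to change.** In Statistical methods {20a}, replace the significance-triggered rule with a pre-specified covariate set limited to the randomization strata and characteristics that SMS cannot change, for example maternal age, education, parity and distance to clinic. State that modifiable enrolment values (parental self-efficacy, depression symptoms and, if collected then, danger-sign knowledge) are used neither as adjustment covariates nor as evidence of baseline imbalance.

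Optionally, use eCHIS messaging data to flag whether a woman's first SMS preceded her enrolment visit. This dates exposure better than a 28-week cut-off, because receipt also depends on consent and sign-up. Restricting baseline reporting to women enrolled before 28 weeks is not advisable: under uniform enrolment it would set aside about 80% of the data for a poor proxy.

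The cost is a change of wording and, if wanted, one derived flag. Recruitment, intervention and data collection stay as they are. A little precision from the excluded questionnaire covariates may be lost. Because analysts are not blinded, the set should be fixed before covariates are compared by arm.
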